### Outcomes

The study will assess the following outcomes to address the main aims. This will be collected at baseline for both groups (before receiving implementation support) and at follow-up (approximately 9-months post intervention). Data collection for all outcomes listed below will be conducted via an online survey (Qualtrics, Utah, United States), unless otherwise stated.

### Fidelity and adoption of action implementation

The backbone teams of both the intervention and control communities will select one representative to report on the fidelity of action implementation at baseline and at follow-up. Although many actions may be identified as part of the systems process, they will be asked to describe one selected action for implementation. Fidelity is assessed via three items with responses on a Likert scale, reporting on i) the extensiveness (1 = not at all to 7 = extensively), and ii) frequency (1 = not at all to 7 = all the time) of action implementation and iii) how engaged (1 = not at all to 7 = all the time) organisation and individuals are with the implementation process. Additionally, the survey will assess adoption of the selected action, which will be measured using three items assessing ‘intention to implement’ the action (on a Likert scale, with 1 = Strongly disagree to 7 = Strongly agree). These items were adapted from previous validated items used by the research team [50].

### Acceptability of implementation strategies

All backbone team members of intervention communities (between 3–8 in each community) will be asked to report on the acceptability of the intervention at follow-up. Acceptability will be defined as the perception amongst the backbone team that the intervention and implementation strategies are agreeable, palatable or satisfactory [51]. This will be assessed using seven items on a five-point Likert scale reporting on the following elements of Action-RESPOND:

Affective attitude (1 = strongly dislike to 5 = strongly like),Burden (1 = no effort at all to 5 = huge effort),Perceived effectiveness (1 = strongly disagree to 5 = strongly agree),Intervention coherence (1 = strongly disagree to 5 = strongly agree),Self-efficacy (1 = not at all confident to 5 = very confident),Opportunity costs (1 = did not have to give up activities to 5 = gave up many activities), andOverall acceptability (1 = completely unacceptable to 5 = completely acceptable).These items are underpinned by the Theoretical Framework of Acceptability [51], a validated framework used to assess the acceptability of healthcare interventions from the perspectives of intervention deliverers and recipients.

### Appropriateness and usefulness of the implementation strategies

At follow-up, the appropriateness of the implementation strategies will be assessed with intervention communities via four items on a Likert-scale (1 = strongly disagree to 5 = strongly agree) and one open-ended item. The backbone team members will also be asked to report on how useful they thought each of the individual implementation strategies were (Likert scale, with 1 = not helpful at all to 5 = extremely helpful) and to qualitatively report on why they rated the components this way.

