		Context: i) Edu Workshop–change over time and implementation CLD building activity ii) Edu Workshop–provision of training and resources (implementation tools and action plan template) and demonstrate application iii) During check-in sessions
		Target: i) Backbone team ii) Backbone team iii) Implementation Champion/s
		Time: i) Edu Workshop (face-to-face, 6-hour) ii) Edu Workshop (face-to-face, 6-hour) iii) Check-in sessions (online meeting, 1.5 hours, approx. 2-months apart)

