*Delivery modality*. Action-RESPOND consist of seven implementation strategies that will be delivered over approximately 9-months via one online meeting (GMB3 debrief), one face-to-face group education workshop (Edu Workshop), two formal facilitation contacts delivered by an implementation coach (Check-in sessions) and local tailored support as requested. Additionally, we will incorporate system science concepts, including qualitative systems mapping, use of reference modes (which capture the dynamic nature of key factors within a system) and feedback loops, during the delivery of the multicomponent implementation strategy (see Table 1). The research team delivering the intervention consists of systems science experts (AB, JH) and implementation scientists (SY, [name]) and an Implementation Coach (MH). The Implementation Coach (MH) has 10 years of health promotion experience working within the targeted communities and is situated within one community of the Ovens-Murray region.

The Edu Workshop will be delivered face-to-face to the ‘backbone team’ who consist of community development workers from local councils, health promotion practitioners from relevant health services and relevant non-government organisations in the region. This session will be co-facilitated by systems science (AB) and implementation science (SY) experts together with the Implementation Coach (MH).

The Implementation Coach (MH) will be primarily responsible for delivering the two facilitation check-in sessions. The sessions will either be delivered over videoconference call or face-to-face (depending on preference of community) with identified Implementation Champion(s) within each community. The Champion/s are likely to consist of one or multiple individuals (in the instance of shared role or part-time staff) who are health promotion officers within the local community health teams or local council.

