### Data management

All data will be collected online and directly entered into the survey platform, and as such no data entry errors are expected. The majority of survey items are close-ended in response and require a response to minimise missing data. The research team will send reminders and follow up on any non-responses to minimise missing data. Given the pilot nature and the small number of participants, a manual check will be undertaken to identify any clear incongruence in responses. If such responses are identified, this will be discussed with the data monitoring committee and relevant actions will be made depending on the type of data and extent of misreporting. This includes clarifying with participants, and/or using previously reported relevant data to inform data imputations. All decisions will be documented and reported in the analysis process. The data collected will be stored on a secured server at Deakin University in accordance with the requirements of all ethics committee. The data monitoring committee comprises of the chief investigators on the grant and the Action-RESPOND team. Personal information of participants (name and contact details) will be stored in a password-protected electronic Excel Spreadsheet. Only research staff approved on the ethics application will have access to this file or any raw data of the study. All results will be reported at the unit of the LGA. The Action-RESPOND team will monitor the progress of the trial, oversee the data collection progress, and provide updates to the data monitoring committee. Reports will be submitted annually to the ethics committee and funding body.

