### Data analysis

All statistical analyses will be undertaken using relevant statistical software. Descriptive statistics (mean and standard deviation (SD) or median and range when non-normal) will be generated for all assessed outcomes. For acceptability, feasibility, appropriates and usefulness, individual scores from each item will be summed (reverse scored where necessary) and combined to provide a score for each community. A score of ≤2 will be considered a negative response, indicating the Action-RESPOND program is considered unacceptable, while ≥4 will be indicative of an acceptable program. For feasibility, ≥4 (higher scores) will indicate greater feasibility, while ≤2 (lower scores) will indicate lower feasibility, consistent the recommendations of Weiner et al (2017) in the Feasibility of Intervention Measure [52]. Answers to the open-ended questions will be analysed qualitatively.

For implementation outcomes (fidelity and adoption of the selected action for implementation), item responses will be summed to provide an overall fidelity and an overall adoption score for both the intervention and control group. This will be compared between groups using a linear regression, controlling for baseline scores. Changes in implementation determinants and adaptations to actions will be described narratively for each community.

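### Usefulness ratings of the coach-led check-in sessions pool the Implementation Champions, who are their stated recipients, with other backbone team members, and the stated scoring does not separate them.

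*Protocol article*

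**What the plan says.** Under *Appropriateness and usefulness of the implementation strategies*, the protocol article states: "The backbone team members will also be asked to report on how useful they thought each of the individual implementation strategies were". The scale runs from 1 to 5, and respondents are also asked to explain their ratings in words. Team size is given under *Acceptability of implementation strategies*: "All backbone team members of intervention communities (between 3–8 in each community".

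Under *Delivery modality*, "Action-RESPOND consist of seven implementation strategies", and the two check-in sessions are held "with identified Implementation Champion(s) within each community". Table 1 makes the same distinction in its row on knowledge and skills: "Target: i) Backbone team ii) Backbone team iii) Implementation Champion/s". Part iii is the problem solving done in the check-ins. The section on strategy 6 (tailored facilitation) also places the check-ins with the champions, and says that every contact and its attendees will be logged in a spreadsheet.

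The number of champions is left open: "The Champion/s are likely to consist of one or multiple individuals". A footnote to Table 1 says that they come from the backbone team, so they are among the raters.

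*Data analysis* lists usefulness among the outcomes for which "individual scores from each item will be summed (reverse scored where necessary) and combined to provide a score for each community". It states no split by who received a strategy.

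**The concern.** For the check-in component, the people asked to rate and the people who receive it are different groups. The whole backbone team is asked how useful each strategy was, but the check-ins go to one or a few of its members. A colleague who did not attend has no direct experience of the sessions to report, and the stated scoring gives that answer the same standing as the champion's.

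Facilitation is the main delivery approach of Action-RESPOND, and the check-ins are its formal coach-led contacts after the workshop. Usefulness is also the only scored outcome in the article that distinguishes one strategy from another, because the acceptability items concern the program as a whole. *Progression criteria* says that the pilot data will help to improve the intervention before a full trial. A diluted check-in rating makes it harder to see whether recipients found the coaching helpful or unhelpful.

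**Working it through.** The plan gives no figure of its own on this point, so there is none to reproduce.

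**Inputs**
- Team size m = 3 to 8 (*Acceptability of implementation strategies*).
- Five intervention communities (*Trial design*), hence 5 × 3 = 15 to 5 × 8 = 40 raters.
- Champions per community c: not fixed by the article. Assumed to be 1, 2 or 3.
- Assumed: every member responds, and only champions attend the check-ins.

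**Step 1: share of check-in ratings from members who are not champions, (m − c)/m**

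| m | c = 1 | c = 2 | c = 3 |
|---|---|---|---|
| 3 | 2/3 = 66.7% | 1/3 = 33.3% | 0% |
| 4 | 3/4 = 75.0% | 2/4 = 50.0% | 1/4 = 25.0% |
| 5 | 4/5 = 80.0% | 3/5 = 60.0% | 2/5 = 40.0% |
| 6 | 5/6 = 83.3% | 4/6 = 66.7% | 3/6 = 50.0% |
| 7 | 6/7 = 85.7% | 5/7 = 71.4% | 4/7 = 57.1% |
| 8 | 7/8 = 87.5% | 6/8 = 75.0% | 5/8 = 62.5% |

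With one champion, the other members form a majority at every team size. With two champions this holds only for teams of five or more, and with three only for teams of seven or eight.

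**Step 2: effect on the team's rating.** Suppose the item is averaged over the team, and the other members' answers do not depend on the champions' experience. If the champions' rating changes by D points, the team mean changes by D × c/m, whatever values the others give. Take the largest possible contrast on the scale, D = 5 − 1 = 4:
- c = 1: 4/3 = 1.33 for m = 3, 4/5 = 0.80 for m = 5, 4/8 = 0.50 for m = 8.
- c = 2: 8/3 = 2.67 for m = 3, 8/5 = 1.60 for m = 5, 8/8 = 1.00 for m = 8.

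If other members repeat what the champion told them, the mean shrinks less, but their ratings are then second-hand.

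**Step 3: raters left if the check-in item is scored by receipt.** 5 × 1 = 5 with one champion per community and 5 × 2 = 10 with two, out of 15 to 40.

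**The case against.** A reader might infer more than the article supports, in five ways.

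- *That non-attendees are forced to guess.* The article says that members are asked to rate. On compulsory answers it says only: "The majority of survey items are close-ended in response and require a response to minimise missing data". That covers most items and does not name these. The questionnaire is not shown, and a required item can still carry a not-applicable answer, so its absence cannot be asserted.
- *That most members never received any coaching.* The coach co-facilitates the workshop for the whole backbone team, and extra support on request is not limited to champions. Non-receipt can be argued only for the formal check-ins.
- *That three of the seven strategies share the problem.* In the narrative list, strategy 3 (feedback to the community) is worked through with champions and strategy 7 (leadership) is aimed at managers. Table 1 names community members and stakeholders as the target of the feedback work. The team can judge whether either helped without being its target. Strategy 7 is meant to win support for the team's own decisions, and restricting its ratings to recipients could leave almost no raters.
- *That pooled scores would miss a cut-off.* The cut-offs of 2 and 4 in *Data analysis* are worded for acceptability and feasibility. None is stated for one strategy's usefulness.
- *That strategies will be kept or dropped on these ratings.* No such rule exists, and *Progression criteria* names fidelity, adoption and acceptability.

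Two mitigating points also stand. Respondents explain their ratings in free text, where a non-attendee can say so, and the attendee log allows a split by receipt without any change of design. Neither is tied to the score in the article, so the narrow point remains.

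**Conclusion.** The point holds for the formal check-in sessions only. The whole team is asked to rate them, the champions receive them, and the stated scoring combines the ratings without regard to receipt. Assuming full response and attendance by champions alone, other members supply 67% to 88% of the ratings with one champion per team and 33% to 75% with two. Whether they are a majority depends on a number of champions that the article does not fix.

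The consequence is a blurred descriptive result for one component, of use mainly in refining the intervention. It does not touch the fidelity comparison or a named progression criterion. It is a minor improvement.

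**What to change.** For the check-in component, state that usefulness will be scored and reported by receipt, with receipt taken from the planned log of contacts and attendees. If the survey does not already have one, add a did-not-take-part response to that item. Report the number of raters per community beside the score. Keep the full backbone team's ratings for strategies 3 and 7.

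The cost is one response option and one sentence on scoring. If the follow-up survey has already been sent out, reporting by receipt is still possible wherever responses can be linked to the log. The downside is that the check-in score will rest on as few as one or two raters per community, which is the amount of first-hand information that exists.

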### Cost

The total cost of delivering the Action-RESPOND program will be estimated, including labour (i.e., research team time, facilitator preparation, administration, and delivery of the program), travel and equipment. A costing tool will be programmed in Microsoft Excel and used to track program delivery costs according to opportunity cost principles. The cost for communities to receive the program will be estimated using administrative records (e.g., attendance records at Edu-workshop and Check-in sessions). The time, travel and equipment cost of supporting the implementation of the prioritised action will be estimated using survey data. Published wage rates will be used to estimate labour costs, and travel and equipment costs will be estimated using market rates.

### Changes in implementation determinants and adaptations to actions

This will be captured in the intervention communities only, via the STICKE software, and include structured data collection (including specific prompts and questions) as part of the Check-in sessions. This can be exported into a Microsoft Excel spreadsheet and will be collated by the research team following each contact with the Implementation Champion of intervention communities. This will capture how existing barriers change, any new barriers and the relationship to the existing barriers, action progress and strategies implemented.

### Potential co-intervention and contamination

At follow-up, we will assess if communities received any other support or new funds to implement their actions (outside of the research team) and to describe this support. Additionally, we will assess the extent of contamination in participants of the control communities, by asking whether they have received any component of the Action-RESPOND program and any other support to deliver the proposed initiatives.

### Co-benefit and adverse outcomes

At follow-up, we will assess if any additional actions were implemented resulting from receiving Action-RESPOND and for participants to describe the specific actions.

We will ask of any other unintended outcomes (both positive and negative) observed by the communities as a part of participating in this trial.

### Sample size

As this is a pilot study, a formal sample-size calculation was not undertaken in line with best practice guidance [38]. However, 10 communities (with between 3–8 representatives) are included, as this number was considered feasible in the timeframe and allocated resources and is sufficient to provide an adequate indication of the feasibility and acceptability of study methods and the sustainment strategy.

### Data management

All data will be collected online and directly entered into the survey platform, and as such no data entry errors are expected. The majority of survey items are close-ended in response and require a response to minimise missing data. The research team will send reminders and follow up on any non-responses to minimise missing data. Given the pilot nature and the small number of participants, a manual check will be undertaken to identify any clear incongruence in responses. If such responses are identified, this will be discussed with the data monitoring committee and relevant actions will be made depending on the type of data and extent of misreporting. This includes clarifying with participants, and/or using previously reported relevant data to inform data imputations. All decisions will be documented and reported in the analysis process. The data collected will be stored on a secured server at Deakin University in accordance with the requirements of all ethics committee. The data monitoring committee comprises of the chief investigators on the grant and the Action-RESPOND team. Personal information of participants (name and contact details) will be stored in a password-protected electronic Excel Spreadsheet. Only research staff approved on the ethics application will have access to this file or any raw data of the study. All results will be reported at the unit of the LGA. The Action-RESPOND team will monitor the progress of the trial, oversee the data collection progress, and provide updates to the data monitoring committee. Reports will be submitted annually to the ethics committee and funding body.

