### Trial design

This pilot RCT (called Action-RESPOND) seeks to build on some of the implementation challenges faced in RESPOND by systematically developing an enhanced implementation support package and assessing the feasibility and potential impact of this with the ten communities already participating in RESPOND. Five communities will receive a multicomponent implementation strategy (intervention) and five will not receive any additional implementation support (control). The trial will assess data at baseline and approximately 9-months follow up (see Fig 1). The reporting of this protocol was consistent with the CONSORT-pilot RCT guidance [38] and the Standards for Reporting Implementation Studies (STARI) statement [39]. Data collection for this trial began in June 2023.

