### Blinding

Action-RESPOND is an open trial, and no blinding was possible due to the nature of the intervention. Therefore, those receiving the intervention were not blinded to group allocation; however, the statistician conducting the data analysis will remain blinded.

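### Fidelity and adoption answers already submitted may be altered by imputation, without the respondent's confirmation, after discussion with a committee that nothing in the protocol masks to arm

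*Protocol article*

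**What the plan says.** All of the rule is in the Data management section of the protocol article. After survey submission, "a manual check will be undertaken to identify any clear incongruence in responses". Answers so identified are discussed with the data monitoring committee, and the action taken depends on the kind of data and how far they appear misreported. Two actions are named, joined by and/or: clarifying with participants, and "using previously reported relevant data to inform data imputations". Decisions are to be documented and reported.

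On membership: "The data monitoring committee comprises of the chief investigators on the grant and the Action-RESPOND team". The Delivery modality text says that the research team, including the Implementation Coach, delivers the intervention. The Blinding section states: "Action-RESPOND is an open trial, and no blinding was possible due to the nature of the intervention". The only role it names as blinded is the statistician who analyses the data.

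For the outcomes concerned, each backbone team "will select one representative to report on the fidelity of action implementation at baseline and at follow-up". "Fidelity is assessed via three items with responses on a Likert scale", each scored 1 to 7; adoption likewise has three 1-to-7 items. Under Data analysis, item responses are summed, and for the group comparison: "This will be compared between groups using a linear regression, controlling for baseline scores".

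**The concern.** The rule applies to answers that were given, not only to missing ones, because what triggers it is suspected misreporting. Since the two actions are joined by and/or, imputation can be used without going back to the respondent. The people who discuss the change are not masked, and some of them appear to have delivered the programme under test. The one protection in the Blinding section, a blinded analyst, acts after the edit and cannot undo it.

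With one rating per community, no within-community averaging dilutes an altered score. Fidelity and adoption estimate the potential impact of the strategies, which is a stated aim of the pilot. They also feed the Progression criteria decision on a larger trial, which core members of the research team take by majority.

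**Working it through.** The protocol gives no power, alpha or SD figure to reproduce (Sample size: no formal calculation), so the check is of leverage.

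**Inputs from the protocol article**
- Communities per arm: 5 (Trial design).
- Ratings per community at each time point: 1 (Fidelity and adoption of action implementation).
- Score: sum of three 1-to-7 items, so the minimum is 3 × 1 = 3 and the maximum 3 × 7 = 21.
- Model: linear regression on group and baseline score (Data analysis). That is 10 observations and 3 parameters, leaving 10 − 3 = 7 residual degrees of freedom; the two-sided 5% critical t is 2.365.

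**Step 1: effect of one edit on the arm mean.** Shift in arm mean, and in the unadjusted group difference, = d/5.

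| Change in one total (d) | Shift |
|---|---|
| 3 | 3/5 = 0.6 |
| 6 | 6/5 = 1.2 |
| 12 | 12/5 = 2.4 |
| 18 (largest possible, 21 − 3) | 18/5 = 3.6 |

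**Step 2: an invented data set, to show what the regression does.** Control: baseline 9, 11, 8, 12, 10; follow-up 11, 12, 10, 13, 11. Intervention: baseline 10, 9, 12, 13, 8; follow-up 15, 14, 15, 7, 13.
- As submitted: adjusted difference 1.51, SE 1.67, p = 0.39.
- With the single follow-up score of 7 replaced by that community's baseline of 13 (d = 6): adjusted difference 2.48, SE 0.63, p = 0.006.
- The unadjusted difference moves from 12.8 − 11.4 = 1.4 to 14.0 − 11.4 = 2.6, which is the 1.2 of Step 1. The adjusted difference moves by 2.48 − 1.51 = 0.97.

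In this example the follow-up outcome for that community is its own covariate value, so its change is zero whatever happened there.

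**Step 3: average size, by simulation (8,000 runs per scenario).** Assumptions, none from the protocol: SD 3 or 4; baseline to follow-up correlation 0.3 or 0.5; baseline mean 10; control follow-up mean 12; true effect 0 or 3 points; scores rounded and held within 3 to 21; two-sided 5% test.
- One intervention score chosen at random and replaced by its baseline: the mean absolute shift in the adjusted difference is 0.57 to 0.80 points with no true effect and 1.05 to 1.11 with a 3-point effect. The p < 0.05 reading changes in about 4% and 12% to 23% of runs respectively.
- Only the intervention community with the largest fall replaced by its baseline, no true effect: significant results favouring the intervention rise from 2.4–2.8% to 3.7–4.2%.

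The direction is not fixed. Selective replacement of a fall favours the intervention. Random replacement under a 3-point effect works against it, because the assumed mean rise in that arm is 2 + 3 = 5 points and losing one community's rise costs on average 5/5 = 1.0 point of unadjusted difference.

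**The case against.** The case on the other side has real content.

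- **Safeguards exist.** Asking the participant is the first action listed, decisions are to be documented and reported, and the trigger is limited to obvious inconsistency. This stands as transparency. It does not require the respondent's confirmation or a result on the data as submitted.
- **Baseline carry-forward is not the stated plan.** A reader might infer that a follow-up answer is simply overwritten by the baseline answer. The text says only that earlier relevant data may inform an imputation, and intervention communities also have check-in records and STICKE exports. Carry-forward is one permitted use, so the reuse of the covariate as outcome in Step 2 is conditional on it.
- **The role of delivery staff is inferred.** Nobody is named as doing the manual check, the Action-RESPOND team is not separately defined, and nothing says that every chief investigator delivers the programme. The inference comes from reading Blinding, Delivery modality and Data management together.
- **Forced response does not make the check needless.** One might argue that imputation has no purpose because closed items require an answer. That prevents blanks, not inconsistent answers, and it covers only most items.
- **The average effect is modest.** Large edits need several items to be far wrong, and the example in Step 2 is invented. This stands.
- **Some detail may sit elsewhere.** Criteria for incongruence and the imputation method could be in an analysis or data management plan that is not shown. Their absence is no fault here. The point rests on what the article expressly permits.

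**Conclusion.** The concern holds as a weakness in a stated rule. Submitted fidelity and adoption answers can be altered without the respondent's confirmation, after discussion with a committee that nothing masks in an open trial, and before the blinded statistician sees them. The size follows from the design alone: d/5 on the arm mean per altered community, at most 3.6 points on a 3-to-21 score. The simulated shifts of roughly 0.6 to 1.1 points for one replaced score rest on the assumed SDs, correlations, means and effects, and on baseline being the earlier data used.

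A reader might infer that bias is established. The documents do not support that: they show an open route, not that it was or will be used, and its direction could go either way. The five-scores-per-arm argument is also confined to fidelity and adoption. Acceptability is reported by 3 to 8 people per intervention community, at follow-up only, and so has no baseline value of its own. As the protocol states no alpha, what is at stake is the estimate and the progression decision, more than a formal test.

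**What to change.** For fidelity and adoption, amend Data management to state that:

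1. the main analysis uses responses as submitted;
2. a value is changed only when the respondent, on being asked, confirms a correction;
3. imputation over submitted answers from earlier reports is deleted;
4. the original value is kept alongside any corrected one;
5. results are reported with and without confirmed corrections.

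Where practicable, decide which answers to query on an extract holding only the fidelity and adoption items, with arm labels and arm-specific items removed. The analysing statistician should not screen the full survey: only intervention communities answer the acceptability, appropriateness and usefulness items, and control communities get the contamination questions, so the full survey would reveal the arm.

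The cost is a few sentences, a small data extract, and adding original values to the record of decisions already promised. The downside is that a few odd responses may remain in the main analysis when the respondent does not confirm a correction.
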